## Methods for statistical analyses

Data will be analyzed on the FAS population. The primary analysis will be performed at the time of accrual of 132 progression or death events in the 220 enrolled patients. The final analysis will be performed when approximately 60% OS maturity is achieved.

Data will be summarized using descriptive statistics as appropriate. Continuous variables will be summarised by the number of observations (n), mean, standard deviation (SD), median, quartiles (Q1 and Q3), minimum, and maximum. Categorical variables will be summarised by frequency counts and percentages for each category.

### Analysis of the primary variable (s)

PFS will be analysed when approximately 132 progression events have occurred in the study (60% maturity). This analysis will address the primary objective of the trial. The updated results will also be provided at the final analysis.

A Kaplan-Meier (KM) plot of PFS will be presented. Summaries of the number and percentage of patients experiencing a PFS event, and the type of event (progression or death) will be provided along with median PFS and 95% confidence interval.

The analysis on PFS will be based on RECIST 1.1 criteria assessed by investigators, and using all scans regardless of whether they were scheduled or not. The estimated PFS rates at 6 months, 12 months and 24 months will be summarised (using the KM curve) for all patients.

The number of patients prematurely censored will be summarised together with baseline prognostic factors of the prematurely censored patients. A patient is defined as prematurely censored if they had not progressed and the latest scan prior to the date of cut off (DCO) was more than one scheduled tumour assessment interval (+ 2 weeks) prior to the DCO date.

### Analysis of the secondary variable(s)

All time to event endpoints will be described as for PFS.

Safety data will be summarised descriptively.

### Subgroup analysis (if applicable)

Subgroup analyses will be performed, as described for the primary analysis of PFS and secondary analysis of OS, to assess the consistency of olaparib effect across potential or expected prognostic factors.

The following subgroups of the PFS and OS may be summarised.

- Response to previous platinum chemotherapy (CR vs PR)
- Time to disease progression on last platinum based chemotherapy received prior to first dose of olaparib (6 – 12 months / > 12 months)
- Measurable versus non-measurable disease at baseline
- *BRCA* mutation type, e.g. germline, somatic *BRCA*; *BRCA1, BRCA2* or *BRCA1/2* (both)
- *HRR* mutation type
- Age at first dose (<65 vs. ≥65)
- Country
- Prior bevacizumab use

Number of prior chemotherapy lines Other baseline variables may also be assessed if there is clinical justification.

### Interim analysis

Interim analysis for OS is planned approximately 3years after last patients enrolled if 60% OS maturity is not achieved by then.

### Exploratory analysis

Biomarker data will be summarized with descriptive statistics. The relationship between biomarkers and treatment effect of olaparib will be explored. The details will be described in the study SAP or a separate exploratory analysis plan.

Due to the retrospective nature of the HRD testing, and that tissue testing for BRCA status will be carried out first, HRD testing will only be possible in those patients with remaining tumour sample/FFPE sample of sufficient quality and quantity. To ascertain whether systematic differences exist between patients with and without necessary tumour sample (or in effect a HRD test), the relation between having a HRD test and patient demographic and clinical characteristics will be investigated using t-tests or chi-squared tests as appropriate for the variable. Participant characteristics will be summarized separately by HRD test using means (SD) and percentages (number).

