## Exploratory objectives

| **Exploratory Objective:** | **Outcome Measure :** |
| --- | --- |
| To explore biomarkers in tumor tissues or blood predictive of sensitivity/resistance to the treatment of olaparib | a) Immune-markers PD-L1 expression in tumor tissues  b) *BRCA* and HRR mutation status in the cell-free DNA from blood samples  c) HRD status in tumor samples  d）Relation between having a HRD test and patient demographic and clinical characteristics |

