## Inclusion criteria

For inclusion in the study patients should fulfil the following criteria:

1. Provision of informed consent prior to any study specific procedures
2. Age 18 years or over
3. Patients with platinum sensitive relapsed high grade (serous or endometrioid) epithelial ovarian cancers (including primary peritoneal and/or fallopian tube cancer)

- Platinum sensitive disease is defined as disease progression ≥6 months after completion of their last dose of platinum based chemotherapy

1. Patients should have received at least 2 previous lines of platinum containing therapy prior to enrolment:

- For the last chemotherapy course immediately prior to enrolment on the study, patients must be, in the opinion of the investigator, in response (partial or complete radiological response according to RECIST 1.1 criteria) and no evidence of a rising CA-125, following completion of this chemotherapy course.
- Pre-treatment CA-125 measurements must meet criterion specified below:
- If the first value is within upper limit of normal (ULN) the patient is eligible to be randomised and a second sample is not required
- If the first value is greater than ULN a second assessment must be performed at least 7 days after the 1st. If the second assessment is ≥ 15% more than the first the patient is not eligible

1. Have availability of 10 ml blood for germline *BRCA*m/HRRm testing and tumor sample for somatic *BRCA*m/HRRm testing: paraffin-embedded archived tumor tissue block (preferred) or, if a block is not possible, it would be better to have qualified 15 5-μm unstained sections.
2. Patients must have normal organ and bone marrow function measured within 28 days prior to administration of study treatment as defined below:

- Haemoglobin ≥ 10.0 g/dL with no blood transfusions in the past 28 days
- Absolute neutrophil count (ANC) ≥ 1.5 x 10^9^/L
- Platelet count ≥ 100 x 10^9^/L
- Total bilirubin ≤ 1.5 x institutional upper limit of normal (ULN)
- Aspartate aminotransferase (AST) (Serum Glutamic Oxaloacetic Transaminase (SGOT)) / Alanine aminotransferase (ALT) (Serum Glutamic Pyruvate Transaminase (SGPT)) ≤ 2.5 x institutional upper limit of normal unless liver metastases are present in which case they must be ≤ 5x ULN
- Patients must have creatinine clearance estimated using the Cockcroft-Gault equation of ≥51 mL/min:

Estimated creatinine clearance = (140-age [years]) x weight (kg) (x F)^a^

serum creatinine (mg/dL) x 72

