## Enrolment/screening period

Procedures will be performed according to the Study Plan in Table 1.

Each potential patient will provide written informed consent prior to any study specific procedures and undergo assessments applicable for the visit.

Patients will have to consent to undergo germline and tumor *BRCA* testing and other non *BRCA* HRR gene panel testing as required.

All patients will be asked to provide consent to perform exploratory analysis. This consent is included in the main patient informed consent form. However consent for providing this sample is optional and will not prevent patients from enrolment into the study. If patients provide consent to perform exploratory analysis, PD-L1 expression of tumor samples, *BRCA* and HRR mutation status in the cell-free DNA from blood samples, and HRD status in tumor samples will be tested after last patient enrolment.

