## Sample size estimate

The sample size of approximately 220 patients is driven by the need to enrol an adequate number of patients to help understand the efficacy and safety of olaparib with the tablet formulation. Around 46 patients with BRCAm ovarian cancer will be enrolled assuming that BRCA mutation rate is 21%.

The primary analysis will be performed after the accumulation of 132 progression or death events which corresponds to 60% maturity. Assuming a median PFS value of 8.4 months, 132 PFS events will provide a 95% confidence interval of (7.1 m, 10.0 m) for the median PFS. Assuming a median PFS of 19.1 months in the BRCA mutated patients, 27 PFS events (60% of 46 BRCA mutated patients) will provide a 95% confidence interval of (13.1 m, 27.9 m) for the median PFS.

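### The t-tests and chi-squared tests planned in 8.5.5 cannot show that HRD-tested patients are representative; differences with 95% confidence intervals should carry that comparison

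*Protocol*

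**What the plan says.** Protocol section 2.4 lists among the exploratory outcome measures "Relation between having a HRD test and patient demographic and clinical characteristics". Section 8.5.5 gives the reason: HRD testing is retrospective, BRCA tissue testing comes first, and "HRD testing will only be possible in those patients with remaining tumour sample/FFPE sample of sufficient quality and quantity". The purpose of the comparison is "To ascertain whether systematic differences exist between patients with and without necessary tumour sample (or in effect a HRD test". The relation with demographic and clinical characteristics "will be investigated using t-tests or chi-squared tests as appropriate for the variable". The section then adds a descriptive element: "Participant characteristics will be summarized separately by HRD test using means (SD) and percentages (number").

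The protocol gives no expected number of tested or untested patients, no significance level for these tests, no size of difference that would matter, and no statement of how a null result is to be read. Section 8.5.5 does leave biomarker detail to the SAP or a separate exploratory plan, but it says so in its paragraph on biomarkers and treatment effect. The tests for this comparison are named in the protocol itself.

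Several provisions bear on who ends up tested:
- Section 3.1 makes tissue an entry condition: "Have availability of 10 ml blood for germline *BRCA*m/HRRm testing and tumor sample for somatic *BRCA*m/HRRm testing".
- Section 4.2 says of the exploratory analyses: "However consent for providing this sample is optional and will not prevent patients from enrolment into the study".
- Section 5.6.4 also assigns remaining tumour tissue to PD-L1 testing.

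**The concern.** The question is whether selection into HRD testing was systematic. A significance test can give evidence that a difference exists. When it is not significant, it cannot establish that a relevant difference is absent, least of all when the group sizes were not chosen for the comparison. Here they are by-products of total enrolment, tissue left after other tests, and optional consent.

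The protocol itself treats response to previous platinum (CR versus PR), BRCA mutation type and number of prior chemotherapy lines as potential or expected prognostic factors (section 8.5.3). An imbalance in any of these between tested and untested patients could make PFS in the HRD-tested patients differ from PFS in the whole trial. If a null p-value were read as reassurance, such an imbalance could be discounted. The opposite error is possible too: with many characteristics tested, an isolated small p-value may be chance.

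**Working it through.** **The plan's own figures.** The protocol states no power or precision for this comparison. Its only precision figures are for median PFS (section 8.2), and they reproduce with median × exp(±1.96/√events):
- 8.4 months, 132 events: 7.08 to 9.96 (stated 7.1 to 10.0).
- 19.1 months, 27 events: 13.10 to 27.85 (stated 13.1 to 27.9).

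**Inputs from the protocol.** Total of about 220 ("The sample size of approximately 220 patients is driven by the need to enrol an adequate number of patients", section 8.2); BRCA mutation rate 21% (section 8.2); t-test or chi-squared test (section 8.5.5).

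**Assumptions, because the protocol is silent.** Two-sided alpha 0.05; number untested varied from 11 to 110; target differences of 0.3 SD, 0.5 SD, 50% tested versus 35% untested (for example, a CR rate), and BRCAm 21% tested versus 36% untested.

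**Formulas.** With u untested and t = 220 − u tested:
- Means: power from the non-central t distribution with u + t − 2 degrees of freedom and non-centrality d/√(1/u + 1/t).
- Proportions: normal approximation with pooled variance under the null.
- Half-width of the 95% CI: 1.96 × √(1/u + 1/t) in SD units, and 1.96 × √(0.25/u + 0.25/t) for a percentage near 50%.

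**Worked case.** With u = 44, √(1/44 + 1/176) = 0.169. For d = 0.3 the non-centrality is 0.3/0.169 = 1.78, giving power 43%, so 57% missed. For d = 0.5 it is 2.97, giving power 84%, so 16% missed.

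**Chance of missing the difference, and CI half-width, N = 220:**

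| Untested | 0.3 SD | 0.5 SD | 50% vs 35% | BRCAm 21% vs 36% | Half-width, SD | Half-width, points |
|---|---|---|---|---|---|---|
| 11 | 84% | 64% | 85% | 75% | 0.61 | 30 |
| 22 | 74% | 40% | 74% | 63% | 0.44 | 22 |
| 33 | 65% | 25% | 65% | 53% | 0.37 | 19 |
| 44 | 57% | 16% | 57% | 45% | 0.33 | 17 |
| 66 | 47% | 8% | 46% | 36% | 0.29 | 14 |
| 110 | 40% | 4% | 38% | 30% | 0.26 | 13 |

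For means the table is symmetric: what counts is the size of the smaller group, whichever it is. The 110:110 row is the best case. Even there, the smallest difference detectable with 80% power is (1.96 + 0.84) × √(2/110) = 0.38 SD.

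**Chance signals.** If k independent characteristics are tested at 5% and no true difference exists, the probability of at least one p < 0.05 is 1 − 0.95^k: 23% for k = 5 and 40% for k = 10. The protocol does not give k, and real characteristics are correlated, so these figures are illustrative.

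**The case against.** The strongest reply has four parts.

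- **No decision rule is written.** A reader might infer from the stated purpose that a non-significant result will be taken to mean no systematic difference. The protocol does not say so; it says only that the relation will be investigated with these tests. This stands. The defect is narrower: significance tests are the only inferential tool named for the question, with no word on how a null result is to be read.
- **The size of an imbalance will be visible.** Means (SD) and percentages by HRD-test status are planned, so a reader will not see p-values alone. This stands too. What the planned output lacks is the uncertainty of each difference.
- **The untested group need not be small.** One might assume that it is, and that this makes the tests weak. The documents do not support that assumption. Tissue availability at entry points to few untested patients; optional consent, BRCA testing first and the competing PD-L1 use point to more. For a 0.5-SD difference the tests perform well once the smaller group has about 44 patients. The point survives because for 0.3 SD or 15 percentage points the miss rate is about 40% even with equal groups.
- **No harm is documented.** A reader might infer that HRD results will be presented as valid for all enrolled patients. Nothing in the protocol says that, and HRD status is not among the named subgroups in section 8.5.3. This limits the weight of the point but does not remove it: the comparison is a listed outcome measure whose named tool does not fully answer its own question.

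**Conclusion.** The point holds as a low-severity improvement. With about 220 patients, a non-significant t-test or chi-squared test cannot show that the HRD-tested subset is representative. A 0.3-SD difference would be missed about 40% of the time at 110:110, 57% with 44 untested and 74% with 22; a 50% versus 35% difference about 38%, 57% and 74%. Large imbalances of 0.5 SD are found with at least 84% power if the smaller group has about 44 patients or more.

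These figures rest on an assumed two-sided 5% level, an assumed range of splits and chosen target differences; the protocol states none of them. The objective is exploratory, and the primary PFS analysis is unaffected.

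**What to change.** In section 8.5.5, or in the exploratory analysis plan that it refers to:

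1. Base the comparison on tested-minus-untested differences, standardised where useful, with 95% confidence intervals. Keep p-values as supplementary at most.
2. State that non-significance is not evidence of similarity.
3. Show Kaplan-Meier PFS for tested and untested patients side by side, as description.
4. Present HRD results as applying to the tested subset.

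Do not attach a tight similarity bound such as ±0.25 SD. The 95% CI half-width is at least 1.96 × √(2/110) = 0.26 SD at any split, so the interval could never fit inside that bound even if the observed difference were zero.

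The cost is a few table columns, one plot and a sentence or two, all from data already collected. The downside is a more cautious statement on representativeness, which is what this sample size supports.

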# STUDY and data MANAGEMENT by astrazeneca

## Training of study site personnel

Before the first patient is entered into the study, a designated AstraZeneca representative will review and discuss the requirements of the Clinical Study Protocol and related documents with the investigational staff and also train them in any study specific procedures and the EDC and/or any other system(s) utilised.

The PI will ensure that appropriate training relevant to the study is given to all of these staff, and that any new information relevant to the performance of this study is forwarded to the staff involved.

The PI will maintain a record of all individuals involved in the study (medical, nursing and other staff).

## Monitoring of the study

During the study, an AstraZeneca representative will have regular contacts with the study site, including visits to:

Provide information and support to the Investigator(s)

Confirm that facilities remain acceptable

Confirm that the investigational team is adhering to the protocol, that data are being accurately and timely recorded in the CRFs, that biological samples are handled in accordance with the Laboratory Manual and that study drug accountability checks are being performed

Perform source data verification (a comparison of the data in the CRFs with the patient’s medical records at the hospital or practice, and other records relevant to the study) including verification of informed consent of participating patients. This will require direct access to all original records for each patient (e.g., clinic charts)

Ensure withdrawal of informed consent to the use of the patient’s biological samples is reported and biological samples are identified and disposed of/destroyed accordingly, and the action is documented, and reported to the patient.

The AstraZeneca representative will be available between visits if the Investigator(s) or other staff at the centre needs information and advice about the study conduct.

### Source data

Refer to the Clinical Study Agreement for location of source data.

### Study agreements

The PI at each/the centre should comply with all the terms, conditions, and obligations of the Clinical Study Agreement, or equivalent, for this study. In the event of any inconsistency between this Clinical Study Protocol and the Clinical Study Agreement, the terms of Clinical Study Protocol shall prevail with respect to the conduct of the study and the treatment of patients and in all other respects, not relating to study conduct or treatment of patients, the terms of the Clinical Study Agreement shall prevail.

Agreements between AstraZeneca and the PI should be in place before any study-related procedures can take place, or patients are enrolled.

### Archiving of study documents

The Investigator follows the principles outlined in the Clinical Study Agreement (CSA).

### Deviation from the clinical study protocol

The Investigator(s) must not deviate from or make any changes to the protocol without documented agreement between the Principal Investigator and AstraZeneca or the IRB approval based on its deliberations.  However, this shall not apply to cases where the deviation or change is necessary to avoid an immediate hazard to the patients or for other compelling medical reasons, or where the changes involve only logistical or administrative aspects of the clinical study (e.g., changes to the organisation/structure of the AstraZeneca, the name/department name of the study site, the address or phone number of the study site or AstraZeneca, the job title of the Investigator, and monitors).

The Investigator(s) should document any deviation from the protocol regardless of their reasons.  Only when the protocol was not followed in order to avoid an immediate hazard to the patients or for other medically compelling reason, the Investigator should prepare and submit the records explaining the reasons thereof to AstraZeneca and the head of study site, and retain a copy of the records.

The Investigator(s) may deviate from or make a change to the protocol without documented agreement between the Principal Investigator and AstraZeneca or the IRB approval, only in the event of a medical emergency, e.g., it is only way to avoid an immediate hazard to the patients.  In such case, the Principal Investigator must notify details of the deviation or change, the reason, and a proposed revision in the protocol if required, to AstraZeneca and the head of the study site and IRB via the head of the study site as soon as possible, in order to obtain their approval.  A certificate of approval by the head of the study site as well as AstraZeneca should be obtained via the head of the study site.

## Study timetable and end of study

The end of the study is defined as ‘the last visit of the last patient undergoing the study’.

There will be a final data cut-off defined as the time when 60% patients achieved overall survival. At this time point, the clinical study database will close to new data. Patients are, however, permitted to continue to receive study treatment beyond the closure of the database if, in the opinion of the Investigator, they are continuing to receive benefit from treatment with olaparib. For patients who do continue to receive treatment beyond the time of this data cut-off, Investigators will continue to report all SAEs to AstraZeneca Patient Safety until 30 days after study treatment is discontinued, in accordance with Section [6.4](#_Reporting_of_serious) (Reporting of Serious Adverse Events). If an Investigator learns of any SAEs, including death, at any time after a patient has completed the study, and he/she considers there is a reasonable possibility that the event is causally related to the investigational product, the Investigator should notify AstraZeneca, Patient Safety. Additionally as stated in Section 6.3 (Recording of adverse events), any SAE or non-serious adverse event that is ongoing at the time of this data cut-off, must be followed up to resolution unless the event is considered by the investigator to be unlikely to resolve, or the patient is lost to follow-up.

The study is expected to start in Q2 2018 and to end by Q2 2024.

The study may be terminated at individual centres if the study procedures are not being performed according to GCP, or if recruitment is slow. AstraZeneca may also terminate the entire study prematurely if concerns for safety arise within this study or in any other study with olaparib.

## Data management by AstraZeneca

Data management will be performed by an AstraZeneca representative, according to the Data Management Plan (DMP)*.*

The data collected through third party sources will be obtained and reconciled against study data.

Adverse events and medical/surgical history will be classified according to the terminology of the latest version the Medical Dictionary for Regulatory Activities (MedDRA). Medications will be classified according to the AstraZeneca Drug Dictionary. All entries to the study database will be available in an audit trail.

The data will be validated as defined in the DMP. Quality control procedures will be applied to each stage of data handling to ensure that all data are reliable and have been processed correctly. The Plans will also clarify the roles and responsibilities of the various functions and personnel involved in the data management process.

When all data have been coded, validated, and locked, clean file will be declared. Any treatment revealing data may thereafter be added and the final database will be locked.

